## Abstract

**Background:**

Long-term management of Parkinson’s disease does not reach its full potential because we lack knowledge about individual variations in clinical presentation and disease progression. Continuous and longitudinal assessments in real-life (ie, within the patients’ own home environment) might fill this knowledge gap.

**Objective:**

The primary aim of the Parkinson@Home study is to evaluate the feasibility and compliance of using multiple wearable sensors to collect clinically relevant data. Our second aim is to address the usability of these data for answering clinical research questions. Finally, we aim to build a database for future validation of novel algorithms applied to sensor-derived data from Parkinson’s patients during daily functioning.

**Methods:**

The Parkinson@Home study is a two-phase observational study involving 1000 Parkinson’s patients and 250 physiotherapists. Disease status is assessed using a short version of the Parkinson's Progression Markers Initiative protocol, performed by certified physiotherapists. Additionally, participants will wear a set of sensors (smartwatch, smartphone, and fall detector), and use these together with a customized smartphone app (Fox Insight), 24/7 for 3 months. The sensors embedded within the smartwatch and fall detector may be used to estimate physical activity, tremor, sleep quality, and falls. Medication intake and fall incidents will be measured via patients’ self-reports in the smartphone app. Phase one will address the feasibility of the study protocol. In phase two, mathematicians will distill relevant summary statistics from the raw sensor signals, which will be compared against the clinical outcomes.

**Results:**

Recruitment of 300 participants for phase one was concluded in March, 2016, and the follow-up period will end in June, 2016. Phase two will include the remaining participants, and will commence in September, 2016.

**Conclusions:**

The Parkinson@Home study is expected to generate new insights into the feasibility of integrating self-collected information from wearable sensors into both daily routines and clinical practices for Parkinson’s patients. This study represents an important step towards building a reliable system that translates and integrates real-life information into clinical decisions, with the long-term aim of delivering personalized disease management support.

**ClinicalTrial:**

ClinicalTrials.gov NCT02474329; https://clinicaltrials.gov/ct2/show/NCT02474329 (Archived at http://www.webcitation.org/6joEc5P1v)

## Introduction

Parkinson’s disease (PD) is a progressive and complex neurological disorder. Patients can experience a wide range of motor symptoms and signs, including bradykinesia, tremor, rigidity, and postural instability. Non-motor symptoms include executive dysfunctions, memory disturbances, attention difficulties, and reduced ability to smell [1-3].

The cornerstone of current therapy is based on the replacement of dopamine, but can also include other drugs that play a role in the activation of dopamine receptors [4]. Although these medications initially have good results in disease management, the effects remain successful for a limited period of time. Most patients eventually develop motor complications, such as the wearing-off effect or dyskinesias [5,6]. Some disease symptoms, such as postural instability and voice/speech impairment, are insufficiently (or sometimes not at all) responsive to dopaminergic therapy.

Two major problems hamper the delivery of optimal individual treatment. First, evaluation of day-to-day variations in a complex disease such as PD is difficult when relying solely upon periodic consultations with experts working in a clinical setting [7]. Even when health professionals use specific and validated instruments, such as the Movement Disorder Society - Unified Parkinson's Disease Rating Scale (MDS-UPDRS) [8], the results represent a subjective and episodic *snapshot* taken under well-controlled conditions, which are usually not representative of the patient’s functioning in daily life. More detailed, objective, and reliable knowledge about real-life functioning would greatly improve the quality of individual medical management. Second, virtually all scientific evidence that is presently available to inform PD management stems from biased clinical studies with short follow-up periods in highly selected sub-populations, who were studied under carefully controlled trial conditions [9,10]. As such, this evidence does not reflect the clinical presentation, treatment response, or disease progression in actual daily life.

To overcome these limitations, wearable sensors are emerging as new tools to continuously and longitudinally obtain information from patients in real-life. The accuracy of sensor data for everyday activity recognition (eg, walking, running) in real-life ranges from 58% to 97% [11]. These sensors, typically consisting of embedded accelerometers, have been used successfully to determine PD-related symptoms [12-16]. However, to date these studies have relied upon small sample sizes (n=5 to 43 participants) and short follow-up periods (3 days to 6 months; see Multimedia Appendix 1).

The primary aim of the Parkinson@Home study is to evaluate the feasibility and patient compliance of using wearable sensors to collect data for at least 3 months in a large patient group. A secondary aim of this study is to address the usability of these data for answering clinically relevant research questions (eg, to determine the relationship between sensor-derived measures and clinical measures). Finally, the study aims to build a database for future development and testing of novel algorithms applied to sensor-derived data from PD patients during daily functioning.

## Methods

### Study Design

The Parkinson@Home study is an observational study involving 1000 patients (from whom data will be recorded) and 250 physiotherapists (who will assist in performing the clinical assessments, and who may act as personal coaches during follow-up). Both patients and therapists will be recruited throughout the Netherlands. The study consists of two phases. Phase one aims to assess the feasibility of deploying wearable sensors in a large PD population (n=300). For this purpose, patients will use a number of wearable devices (Pebble smartwatch, Android smartphone, and fall detector) in combination with a customized app (Fox Insight). Follow-up will occur after 3 months (13 weeks), starting from the moment the first data are streamed to the server. In addition to using wearable devices, participants will attend a one-time consultation, during which a detailed clinical assessment will be performed by an experienced physiotherapist or a research team member. This clinical assessment will take place in week 7, or later during the follow-up period. Phase two, which will include an additional 700 participants, aims to collect raw sensor data in order to investigate the usability of these data for answering clinical research questions. This phase will also be used to build a database for future validation of novel algorithms applied to sensor-derived data from PD patients during daily functioning. Patients involved in phase one can also be included in phase two if they wish. Data collection for clinical results and device-based outcomes, as well as the follow-up period, will be identical to phase one. To ensure the success of the raw data collection during phase two, devices and raw data collection strategies used in this phase will be chosen after the evaluation of data collected during phase one.

The study protocol was successfully piloted prior to full study implementation to ensure methodological feasibility. In total 20 Dutch PD patients participated in this pilot, using a set of wearable devices (one smartphone and one smartwatch) and the Fox Insight app. The patients were asked to use these devices for 24 hours, seven days a week, and were followed for four weeks. In total, 58% of patients that were approached agreed to participate. Some patients were reluctant to manage technology and to deal with possible technical problems, which caused them to refrain from participation. All participants (except for two) needed at least one support call for device troubleshooting. Streaming compliance for the sensor data was 88%.

### Inclusion and Exclusion Criteria

#### Patients

The inclusion and exclusion criteria for patients will be kept purposefully broad, in order to represent the full diversity of real-life PD experiences. Inclusion criteria specify that patients must be 30 years of age or older, and be diagnosed with PD by a physician. No exclusion criteria will be applied.

#### Physiotherapists

Physiotherapists who are members of the Dutch ParkinsonNet [17,18] are eligible to participate. ParkinsonNet physiotherapists have received several PD-specific educational training programs, and treat a high number of PD patients each year. Physiotherapists who want to participate should take the official MDS-UPDRS course (provided online by MDS [19], and further in person training provided by the research team) and be able to include and/or assess an average of four PD patients for the study.

### Patient Recruitment Process

We will apply an incremental recruitment strategy. Initially, we will only include patients that already possess a compatible Android/iPhone smartphone. Subsequently, and only if needed, we will include patients that do not possess a smartphone; these patients will be provided with a loaned smartphone device. The reason for this incremental approach is that patients with their own device will likely require less technical support from the research team, as was the case in our pilot study. This strategy will increase the feasibility of complete data collection in a total of 1000 patients.

Patients will be recruited both in the community and through their treating physiotherapists. To reach potential participants in the community, we will use a number of communication channels: (1) the ParkinsonConnect community, an online community for Parkinson’s patients and healthcare professionals involved in their care [18]; (2) the webpage of the Dutch Parkinson Patient Association; (3) an article in the magazine of the Dutch Parkinson Patient Association; (4) presentations about the study to local patient support groups (*Parkinson Cafés*); (5) promotional material for patients will be sent to all ParkinsonNet physiotherapists (approximately 990 individuals), regardless of whether they participate in the study or not, and we will ask them to recruit patients within their practice; and (6) via a study website [20] which provides information about the study. The study website offers both patients and physiotherapists the possibility to sign up for the study online.

After signing up for the study, potential participants will be contacted by phone by a member of the research team, who will provide additional information about the study and check eligibility. If respondents are eligible and willing to participate, they will receive an informed consent form. After the informed consent form has been signed digitally, the research team will provide the participant with all necessary devices and user manuals.

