### Data Analyses

#### Phase One

Feasibility and compliance will be addressed using descriptive analyses. For feasibility, the primary outcomes will include the total support time per participant, the number and rate of drop-outs, usability of the system, bias within recruitment strategies, and the type of problems faced by patients. Regarding compliance, the outcome measures include the total hours of sensor data collected per participant, the number of compliant days, and the percentage of time that sensor data were streamed during the follow-up period.

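### Phase one takes smartphone owners first because they should need less support, so its primary support-time outcome is likely to be lower than in the intended Parkinson's population

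*Protocol article*

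**What the plan says.** Under Inclusion and Exclusion Criteria (Patients), entry requires age 30 or older and a physician's diagnosis of Parkinson's disease. The criteria are deliberately broad so that the sample reflects the full variety of the disease, and "No exclusion criteria will be applied". Study Design describes phase one (n=300) as a test of whether wearable sensors can be deployed in a large population with the disease. It also says that the phase-two devices and raw-data strategy will be chosen after the phase-one data have been evaluated.

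The Methods section on the patient recruitment process then sets an order of entry: "Initially, we will only include patients that already possess a compatible Android/iPhone smartphone". The second step is conditional: "Subsequently, and only if needed, we will include patients that do not possess a smartphone", and these patients receive a loaned phone. The stated reason is that "patients with their own device will likely require less technical support from the research team, as was the case in our pilot study". The stated benefit is complete data collection in 1000 patients.

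The plan for analysing phase one is descriptive throughout. Its list of feasibility measures opens as follows: "the primary outcomes will include the total support time per participant, the number and rate of drop-outs". Also listed are usability, "bias within recruitment strategies" and the type of problems that patients meet.

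**The concern.** The order of entry depends on a characteristic that the authors themselves expect to reduce support need, and support time is a primary outcome. The direction of the selection effect on that outcome is therefore given by the article's own rationale.

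Phase one is the study's answer to its primary aim, and it informs the choice of devices for phase two. If nearly all phase-one participants own a phone, the support time reported describes people already used to such a device. Someone planning helpline capacity for a general Parkinson's population from that figure would probably plan too little.

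**Working it through.** The article states no figure for this effect, so there is none to reproduce. The check has three parts: whether the sections connect, whether the loan-phone step was likely to be used in phase one, and what can be said about size.

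**1. The sections side by side**

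- Intended population: the full variety of people with Parkinson's disease (Inclusion and Exclusion Criteria; Study Design).
- Order of entry: owners first, non-owners conditionally (Methods, Patient Recruitment Process).
- Reason for the order: owners need less technical support, with the pilot cited (same section).
- Outcome: total support time per participant is primary (Data Analyses, Phase One).

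For support time, every link is in the text. For drop-out, usability and compliance, nothing in the article links the outcome to phone ownership. The pilot paragraph in Study Design says that some patients declined because they were reluctant to manage technology. That concerns refusal before entry and is not split by ownership.

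**2. Was the loan-phone step likely to be triggered in phase one?**

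Inputs (Results, Patient Recruitment Process): 1164 applications, 342 invited for phase one, 300 included, 734 on the waiting list for phase two.

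- Uptake: 300/342 = 87.7%, which matches the article.
- Applications per phase-one place: 1164/300 = 3.9.
- Share of applicants invited: 342/1164 = 29.4%. At the observed uptake, owners alone could have filled phase one if at least 29.4% of applicants had a compatible phone. This treats all applications as available from the start. They arrived over eight months, so the true threshold could be higher.
- Study-wide, the margin is far smaller: 1164/1000 = 1.16 applications per place. At the same uptake the waiting list gives 734 × 0.877 = 644 participants, short of the 700 additional participants planned, although phase-one patients may also join phase two.

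The loan-phone step may thus hardly have been used in phase one, while it could well be needed later. The article does not say how many of the 300 had loaned phones, and Table 1 splits applicants and participants by recruitment channel, not by ownership.

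**3. Size**

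Let s be the share of owners in the intended population and R the ratio of mean support time in non-owners to that in owners. An owner-only sample then shows 1/(s + (1 − s)R) of the population mean. Neither s nor R is in the article, so the values below are assumptions.

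| s | R | s + (1 − s)R | Understatement of mean support time |
|---|---|---|---|
| 0.7 | 1.25 | 1.075 | 7% |
| 0.5 | 2 | 1.5 | 33% |
| 0.3 | 3 | 2.4 | 58% |

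At R = 1 the understatement is zero, and any loaned-phone users among the 300 would reduce it. The table shows only that the effect could be small or large. The pilot's 18 of 20 patients (90%) with at least one support call does not narrow it, because that figure is not split by ownership.

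**The case against.** The strongest reply is that the order of entry is an open, reasoned trade-off informed by the pilot. Recruitment bias is itself a primary feasibility outcome, the Discussion says that avoiding selection bias will be a challenge, the analysis is descriptive, and the article states no success threshold that a favourable figure could wrongly pass. Much of this stands, and it limits how serious the point is. It does not remove it. Describing recruitment bias cannot supply support times for non-owners who were never enrolled, and the Discussion's only remedies are patients' willingness to learn and an efficient support model.

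A second reply is that a table by phone ownership is detail that an article may leave to the full plan. That is fair for the table alone. The point, however, rests on a stated recruitment rule set against a stated primary outcome and a stated target population, not on a missing table.

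A reader might also infer more than the article supports:

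- **That ownership is a hidden exclusion criterion.** It is not. The plan provides loaned phones, so this is an order of recruitment. Writing ownership into the eligibility criteria would misstate the plan.
- **That every feasibility and compliance outcome will look too good.** The article ties ownership to technical support only. The rest is plausible inference.
- **That non-owners are the main challenge named in the Discussion.** The Discussion speaks of elderly people's inexperience with technical devices, as a second challenge, and does not mention ownership.
- **That ample applications make the loan-phone step redundant throughout.** The ratio of 3.9 holds for phase one only.
- **That phase two must drop the owners-first order.** That is a question of helpline and loan-phone resources, on which the sponsor may reasonably choose either way.

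**Conclusion.** The point holds for phase-one support time. If the recruitment order was followed as written, that outcome is likely to be lower than in the population that the eligibility section describes. The direction rests on the article's own statement about owners. It also assumes that few loaned phones were issued in phase one, which the recruitment figures make plausible but the article does not confirm.

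The size is unknown. The 7% to 58% range follows entirely from assumed inputs and should not be cited as an estimate. No direction is documented for drop-out, usability or compliance.

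The phase-one data remain usable. What needs care is the population to which the feasibility conclusion is applied.

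**What to change.** - At the existing telephone eligibility check, record for every applicant whether he or she owns a compatible smartphone. For phase-one participants already enrolled, establish who used a loaned phone.
- Under Data Analyses, Phase One, state that support time, drop-out, usability and compliance will be reported separately for own-phone and loaned-phone participants.
- Under the recruitment-bias outcome, compare ownership between applicants and participants.
- If few or no loaned-phone participants were enrolled, limit the phase-one feasibility conclusion to patients who own a compatible smartphone.

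The cost is one extra question, one extra descriptive table and a narrower phase-one claim. The eligibility criteria and the order of recruitment can stay as they are.

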### Recruitment and Training of Physiotherapists

All ParkinsonNet physiotherapists will be contacted by email to inquire about study participation. Should this email not result in adequate numbers of participating physiotherapists, we will personally contact ParkinsonNet physiotherapists by telephone. As with the recruitment process for patients, after signing up via the study website, physiotherapists will be contacted by email or phone to check eligibility.

Once included, physiotherapists must pass the online MDS-UPDRS training successfully [19], as required by the International Parkinson and Movement Disorder Society, which allows them to perform the MDS-UPDRS [8]. After successful completion of the training, physiotherapists will participate in one face-to-face training session, in which they will assess one patient, in order to practice the MDS-UPDRS assessment and consolidate their understanding of the assessment process and study procedures.

### Ethical Aspects and Trial Registration

This study will be conducted in compliance with the Ethical Principles for Medical Research Involving Human Subjects, as defined in the Declaration of Helsinki. The study protocol and communication materials have been approved by the local ethics committee (Commissie Mensgebonden Onderzoek, Arnhem-Nijmegen; NL53034.091.15).

Consent will be obtained by the research team through an innovative online procedure, which includes a compulsory cooling-off period in a digital environment. When the patient is deemed eligible (eg, meets the inclusion criteria specified in the online sign-up form), an information letter and consent form will be send by email. The research team and an independent physician can be approached for questions and verbal explanation. Next, the potential participant has the possibility to confirm participation digitally, via a new URL sent to him/her by email after 48 hours. The URL redirects the patient to the study webpage, where he/she can confirm that they have read all information and that they agree to participate. As recommended by the ethics committee, this final step is blocked for 48 hours after the first email has been sent, to ensure that potential participants take time to consider participation. After the agreement to participate, the participant will see a confirmation message on the study webpage. No signature or scanning of documents will be necessary at this point. The Parkinson@Home study is registered in the ClinicalTrials.gov registry (NCT02474329) [21].

### Wearable Sensors Phase One

#### Pebble Smartwatch

The Pebble is a commercially available smartwatch, with a variety of embedded sensors, such as tri-axial accelerometer, light sensor, and magnetometer. Accelerometers are able to record acceleration along three orthogonal spatial axes, producing acceleration vectors as single data points, and up to 100 acceleration data vectors can be recorded per second. The Pebble smartwatch operating software allows access to the unprocessed *raw* accelerometer data vectors, creating the opportunity for subsequent analyses of this sensor data. In order to obtain continuous accelerometer data, the Fox Insight app will be installed on each smartwatch. The app enables streaming of the accelerometer data to the smartphone, with a sampling frequency of 50 data vectors per second, using the built-in Bluetooth radios of both the smartwatch and smartphone.

